**Table 2: Dosimetric Parameters of the PBM Device**

| **Parameter** | **PBM Red** | **PBM Infrared** |
| --- | --- | --- |
| Central Wavelength [nm] | 660 | 850 |
| Spectral Bandwidth (FWHM) [nm] | 19 | 30 |
| Operation Mode | Continuous | Continuous |
| Radiant Power per LED [mW] | 28.5 | 23 |
| Number of LEDs | 159 | 159 |
| Total Radiant Power [mW] | 4531.5 | 3657 |
| Energy per LED [J] | 17 | 14 |
| Polarization | Random | Random |
| Aperture Diameter per LED [mm] | 3 | 3 |
| Irradiance at Aperture [mW/cm²] | 20.4 | 16.5 |
| Beam Profile | Multimode | Multimode |
| Exposure Time (s) | 600 | 600 |
| Radiant Exposure per LED [J/cm²] | 12 | 10 |
| Radiant Energy per Session [J] | 2719 | 2194 |
| Application Mode | Direct contact with the skin |  |
| Session Frequency | Once daily for 12 weeks |  |

**4.13 Daily Telephone Follow-Up**

Three medical residents will conduct daily telephone follow-ups with participants to monitor the use of the PBM device, provide guidance, address questions, and record data on spontaneous and nighttime pain, as well as analgesic use. The first contact will be made via video call to reiterate instructions on equipment positioning and use.

During the first five days, participants will specifically be asked about their use of dipyrone 1g orally every 6 hours and tramadol hydrochloride 50 mg orally every 8 hours (prescribed for use as needed).

In addition to monitoring usage and outcomes, the telephone follow-up aims to improve participant adherence. During these calls, participants can ask questions or request additional guidance. The research team will only contact participants after they have been discharged from the hospital, after receiving all instructions and signing the informed consent form (TCLE) in person.

The form template for this evaluation is included in **Appendix 2**, and the commitment form for equipment delivery is provided in **Appendix 10**.

A single cell phone, with a number exclusively designated for the project, will be kept at the hospital. Text or voice messages will not include sensitive data and will be deleted upon project completion.

**4.14 Intervention Failure**

Therapy failure will be characterized if any of the following occurs:

1. Inability to apply PBM daily.
2. The participant develops bleeding, sepsis, urticaria, or any discomfort justifying the discontinuation of PBM or placebo PBM.
3. Discontinuation of treatment for any other reason. In these cases, data collected up to that point will be included in the statistical analysis using a mixed-effects regression model.
4. Failure to attend in-person evaluations or respond to scheduled virtual contacts. Data collected up to this point will also be included in the statistical analysis using a mixed-effects regression model.

**4.15 Outcome Evaluation**

**4.15.1 QuickDASH Questionnaire (Disabilities of the Arm, Shoulder, and Hand)**

This study will use the dysfunction/symptom component of the QuickDASH score, validated for Brazil, available online, and included in **Appendix 1** and **Appendices 3 to 8**. (<https://dash.iwh.on.ca/sites/dash/public/translations/Scoring_QuickDASH_Portuguese_Brazil.pdf>).

The Dysfunction and Symptom Score will be calculated according to the instructions provided online, as follows:

- At least 10 out of 11 items must be answered.
- Each answered question will have a maximum value of 5.
- Scores will be transformed to a 100-point scale by subtracting 1 and multiplying by 25. This transformation facilitates comparison with other 0–100 scales. A higher score indicates greater dysfunction.

**QuickDASH Score Calculation**:

QuickDASH Score=[(Sum of responsesn)−1]×25\text{QuickDASH Score} = \left[\left(\frac{\text{Sum of responses}}{n}\right) - 1\right] \times 25QuickDASH Score=[(nSum of responses​)−1]×25

Where nnn is the number of answered questions.

The QuickDASH will be administered at 1, 2, 4, 8, and 12 weeks post-surgery.

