**São Paulo, SP**

**2023**

**ABSTRACT**

Among the various complications of the postoperative evolution of fractures of the proximal humerus (FUP) are pain and joint stiffness, generating significant functional limitation in the affected limb. Physical therapy is the standard treatment for both surgical and non-surgical cases. Studies have shown positive effects of photobiomodulation (PBM) on repair and regeneration of fractures, as well as on analgesia and functional improvement. However, they suggest standardization and additional evidence. This randomized controlled double-blind clinical study will aim to evaluate the effects of PBM on the functional recovery of participants with FUP surgically treated with special locking plates. The 42 participants will be randomized (1:1) into 2 groups, the Control group (standardized physiotherapy treatment associated with simulated PBM) and the PBM group (standardized physiotherapy treatment associated with active PBM). The PBM will be applied by the participant at home every day, for 10 minutes, using a device containing 318 LEDs light emitting diodes, 159 LEDs of 660 nm (28.5 mW; 12 J/cm2; 17 J per LED) and 159 850 nm LEDs (23 mW; 10 J/cm2; 14 J per LED). The PBM and physiotherapy sessions (30 minutes, 2 times a week) will be held for 12 weeks. Participants will not be aware of their allocation and will be assessed at 24h, 1, 2, 4, 8 and 12 weeks after the surgical procedure by 4 examiners who are also blinded to each participant's allocation. The main outcome, evaluated in all experimental periods, will be the recovery of shoulder function using the Quick-DASH functional scale. Secondary outcomes will be assessments of range of motion of the shoulder using a digital goniometer, quality of life using the SF-6 questionnaire and the occurrence of adverse effects in all experimental periods. Spontaneous pain, pressure pain (dolorimeter), nocturnal pain and the use of analgesics will be evaluated at 1, 2, 4, 8 and 12 weeks; consolidation of fractures at 4, 8 and 12 weeks through radiographic examinations; and muscle strength by progressive weight bearing at 8 and 12 weeks. In addition to punctual evaluations, each participant will be monitored daily through telephone contact. The collected data will be stored, organized in a repository and the appropriate statistical tests will be applied for each specific analysis. In all tests, a significance level of 5% will be adopted.

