**4.12 Photobiomodulation (PBM) Application**

PBM will be administered using LED devices in the form of a shoulder brace. Applications will commence 24 hours after surgery and will continue daily throughout the experimental period. Participants will perform the applications at home, receiving guidance on how to wear and operate the equipment upon hospital discharge, along with written instructions (Appendix 9). Each application will last 10 minutes.

The shoulder brace, manufactured by Cosmedical (Mauá, SP, Brazil), contains 159 red LEDs and 159 infrared LEDs arranged alternately. The area corresponding to the fixation plate, with a 2 cm safety margin added along its entire length, will not be irradiated (LEDs will not be placed there) to avoid potential heating of the plate from energy absorption.

Participants allocated to the control group will receive a device identical to the active one. However, only the activation plug light and sound will turn on when the button is pressed, leaving the internal LEDs deactivated

[figure not shown]

Figure . Design (A) and model (B) of the shoulder brace for PBM application.

Literature reports on the use of PBM after bone fractures indicate the use of red and infrared light sources with varying dosimetric parameters (Table 1), with radiant exposures ranging from 3 to 16 J/cm². The study by Chang et al. (2014), which served as the basis for the sample size calculation in this project, demonstrated positive effects of PBM on functional recovery of wrist and hand fractures using the Quick DASH questionnaire, with a radiant exposure of 9.7 J/cm². Accordingly, this project adopted radiant exposures of 10 J/cm² and 12 J/cm²

| **Wavelength (nm)** | **Power (mW)** | **Irradiance (mW/cm²)** | **Time (sec)** | **Radiant Exposure (J/cm²)** | **Radiant Energy (J) per Point** | **Number of Applications** | **Application Points** | **Results** | **Authors** |
| --- | --- | --- | --- | --- | --- | --- | --- | --- | --- |
| 830 | - | - | - | 8 and 16 | - | Once per day | Sensitive points | Earlier symptom resolution and ambulation | Chauhan & Sarin (2005) |
| 830 | 60 (average power) | 16.2 ± 1 | 600 | 9.7 | 2.5 | 10 | 1 | Pain relief and improved consolidation in conservative wrist fracture treatment | Chang et al. (2014) |
| 808 & 650 | 300 & 100 | 30 ± 20 | 20 ± 30 | 6 ± 3 | 6 ± 3 | 1 | 10 to 12 | Less opioid consumption in tibia fracture treatment | Nesioonpour et al. (2014) |

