**4.15.2 Range of Motion**

Shoulder range of motion (ROM) will be assessed on both sides with the participant in an upright position. The maximum tolerated positions in extension, flexion, abduction, adduction, lateral rotation, and medial rotation will be recorded by the evaluator (Figure 9). Rotations will be assessed at 0° abduction and flexion (Gracitelli, 2015; Tenor Junior et al., 2016). All measurements will be performed using a digital goniometer (Kaptron 360, Shenzhen, Dongguan, China).

[figure not shown]

[figure not shown]

[figure not shown]

[figure not shown]

[figure not shown]

[figure not shown]

[figure not shown]

[figure not shown]

[figure not shown]

[figure not shown]

E

A

B

C

D

[figure not shown]

[figure not shown]

F

**Figure.** Measurement of range of motion (ROM) using a digital goniometer during flexion (A), extension (B), abduction (C), adduction (D), lateral rotation (E), and medial rotation (F), with the goniometer in position.

The ROM assessment will be performed 1 day after surgery and subsequently at 1 and 2 weeks through passive movements. During evaluations at 4, 8, and 12 weeks, active movements will be assessed. Results will be recorded on the corresponding clinical forms for each experimental period (**Appendices 3 to 8**).

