**4.15.6 Quality of Life**

Quality of life will be evaluated using the SF-6 instrument from 2002 (Appendix 3) in its version adapted for use in Brazil (Campolina et al., 2011). Assessments will take place at 1, 2, 4, 8, and 12 weeks, with results recorded in the respective clinical forms (Appendices 3 to 8) for each experimental period.

In the most recent Brazilian version of SF-6 (2002), as in the original, six items are included:

- Functional capacity (items 1, 2, and 10)
- Global limitation (item 3 for physical aspects and item 2 for emotional aspects)
- Social aspects (item 2)
- Pain (all items)
- Mental health (item 1)
- Vitality (item 2) (Campolina et al., 2011).

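### The Abstract includes a 24-hour QuickDASH and SF-6 but sections 4.15.1 and 4.15.6 start both at week 1, so as written every primary-outcome score follows the start of treatment

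*Protocol*

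**What the plan says.** The Abstract states that participants "will be assessed at 24h, 1, 2, 4, 8 and 12 weeks after the surgical procedure", which is six occasions. It then says "The main outcome, evaluated in all experimental periods, will be the recovery of shoulder function using the Quick-DASH functional scale". It also lists SF-6 quality of life among the outcomes measured in all periods.

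Section 4.15.1, under QuickDASH Score Calculation, gives five occasions: "The QuickDASH will be administered at 1, 2, 4, 8, and 12 weeks post-surgery". Section 4.15.6 gives the same five for SF-6. Neither includes 24 h.

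Section 4.15.1 also says that the questionnaire is "included in Appendix 1 and Appendices 3 to 8". Appendices 3 to 8 are six forms. Section 4.15.2 uses the same six for range of motion and does have a day-1 measurement: "The ROM assessment will be performed 1 day after surgery and subsequently at 1 and 2 weeks through passive movements", followed by weeks 4, 8 and 12.

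On treatment start, section 4.12 says "Applications will commence 24 hours after surgery and will continue daily throughout the experimental period". Section 4.7 has the allocation envelope opened 24 h after surgery, when the device is delivered. The text shown plans no preoperative QuickDASH.

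**The concern.** The two schedules differ by one occasion, and it is the only one that could precede treatment. Under section 4.15.1 the first QuickDASH comes at week 1, after about six days of daily active or sham applications. A week-1 score may already carry a treatment effect, so it cannot serve as a baseline.

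The aim is functional recovery, the trial has 42 participants, and section 4.7 describes blocks of six with no stratification. In a trial of this size a pre-treatment value of the primary outcome is useful for two things: seeing whether the arms started alike, and removing some of the between-person variance. If staff follow section 4.15.1, the value cannot be recovered afterwards.

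**Working it through.** **Schedules side by side**

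| Source | QuickDASH | SF-6 | Range of motion |
| --- | --- | --- | --- |
| Abstract | 24 h; weeks 1, 2, 4, 8, 12 | same six | same six |
| Sections 4.15.1, 4.15.6, 4.15.2 | weeks 1, 2, 4, 8, 12 | weeks 1, 2, 4, 8, 12 | day 1; weeks 1, 2, 4, 8, 12 |

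The Abstract and the body agree on range of motion and disagree on both questionnaires.

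**What the forms show.** Section 4.15.3 assigns Appendices 7 and 8 to weeks 8 and 12. Counting back over six visits makes Appendix 3 the 24 h form, so listing QuickDASH on Appendices 3 to 8 suggests a 24 h administration. This is an inference only. The appendices are not shown, and section 4.15.6 cites the same six forms for SF-6 beside a five-occasion schedule.

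**Evaluable number.** Section 4.5 gives 21 per arm, 5% significance, 90% power and 15% loss. It gives no difference or SD, so the figure of 42 cannot be reproduced. Working back, 18 per arm is consistent with it: 18 / 0.85 = 21.2 and 18 × 1.15 = 20.7.

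**Detectable effect without a baseline.** For a two-sided 5% test (two-sided is assumed) with 90% power and 18 per arm:
- normal approximation: (1.960 + 1.282) × √(2/18) = 1.08 SD
- t test: 1.11 SD

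**Effect of adjustment.** A baseline covariate with correlation r to the outcome multiplies the residual variance by 1 − r², and so the detectable effect by √(1 − r²). The documents give no r; the values below are assumptions.

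| r | 1 − r² | Equivalent gain in participants, 1/(1 − r²) − 1 | Detectable effect (t test) | Power at an effect of 1.11 SD |
| --- | --- | --- | --- | --- |
| none | 1 | – | 1.11 SD | 90% |
| 0.2 | 0.96 | 4% | 1.112 × 0.980 = 1.09 SD | 91.1% |
| 0.3 | 0.91 | 10% | 1.112 × 0.954 = 1.06 SD | 92.5% |
| 0.5 | 0.75 | 33% | 1.112 × 0.866 = 0.96 SD | 96.3% |

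This treats one follow-up time as the outcome; it is a guide to size, not a calculation for a repeated-measures analysis.

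**Chance imbalance.** With 21 per arm, the 95% range of a chance baseline difference is ±1.96 × √(2/21) = ±0.60 SD. Without a 24 h score, such a difference on QuickDASH would not be seen.

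**The case against.** The strongest reply is that the body may be right and the Abstract wrong. In the body both questionnaires start at week 1, while range of motion and pain start at day 1, which could be deliberate. The protocol's background section says that the parent DASH asks about the past week. At 24 h that window spans surgery, the sling and possibly days before the injury. The Abstract is also unreliable on timing elsewhere: it starts spontaneous and pressure pain at week 1, while section 4.15.4 collects both on day 1. This stands as a reason to expect a modest correlation and to avoid change scores. It does not remove the contradiction.

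Four stronger readings are tempting and are not supported:

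- **That the comparison is biased without a baseline.** Randomisation keeps a comparison of follow-up scores unbiased.
- **That a chance imbalance could not be corrected at all.** Day-1 range of motion and pain, age and fracture class remain usable as covariates. Only the QuickDASH score itself would be missing.
- **That a planned analysis is broken.** The protocol states no baseline-adjusted analysis. Section 4.14 mentions a mixed-effects model only for discontinued treatment and missed assessments. Covariates are commonly left to a statistical analysis plan, which may exist.
- **That the Abstract's schedule guarantees a pre-treatment value.** The 24 h assessment, the envelope opening and the first application share a time point, and the text does not fix their order.

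**Conclusion.** The contradiction is real and concerns the primary outcome: six occasions in the Abstract, five in section 4.15.1, with the same mismatch for SF-6. The Abstract's wording is enough to establish it; the form numbering only supports it.

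Following section 4.15.1 costs precision and a balance check, not validity. The gain from adjustment is about 1 to 2.5 percentage points of power at r = 0.2 to 0.3, and about 6 at r = 0.5. It is smaller if 24 h scores bunch near the top of the scale, which is plausible one day after surgery with the arm in a sling. These figures rest on an assumed correlation, an inferred 18 per arm and a two-sided test. The point should be settled before recruitment because it is cheap to fix and a missed baseline cannot be collected later.

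**What to change.** 1. Make the Abstract and sections 4.15.1 and 4.15.6 agree by keeping QuickDASH and SF-6 at 24 h.
2. State that both are completed before the allocation envelope is opened and before the device is first used.
3. Name the 24 h QuickDASH as a covariate in the primary analysis, in the protocol or the statistical analysis plan. Do not use it to form change scores, given the one-week recall.
4. Adjust range of motion and pain likewise for the day-1 values that sections 4.15.2 and 4.15.4 already collect, with the same order of measurement before first use.

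The cost is an 11-item questionnaire and the SF-6 items at a visit that already takes place, plus a few lines of text. If the sponsor decides that a 24 h questionnaire is not meaningful, the Abstract should be corrected instead, and the protocol should say that the primary outcome has no pre-treatment value.

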**4.15.2 Range of Motion**

Shoulder range of motion (ROM) will be assessed on both sides with the participant in an upright position. The maximum tolerated positions in extension, flexion, abduction, adduction, lateral rotation, and medial rotation will be recorded by the evaluator (Figure 9). Rotations will be assessed at 0° abduction and flexion (Gracitelli, 2015; Tenor Junior et al., 2016). All measurements will be performed using a digital goniometer (Kaptron 360, Shenzhen, Dongguan, China).

[figure not shown]

[figure not shown]

[figure not shown]

[figure not shown]

[figure not shown]

[figure not shown]

[figure not shown]

[figure not shown]

[figure not shown]

[figure not shown]

E

A

B

C

D

[figure not shown]

[figure not shown]

F

**Figure.** Measurement of range of motion (ROM) using a digital goniometer during flexion (A), extension (B), abduction (C), adduction (D), lateral rotation (E), and medial rotation (F), with the goniometer in position.

The ROM assessment will be performed 1 day after surgery and subsequently at 1 and 2 weeks through passive movements. During evaluations at 4, 8, and 12 weeks, active movements will be assessed. Results will be recorded on the corresponding clinical forms for each experimental period (**Appendices 3 to 8**).

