**4.11 Physiotherapy**

All participants will follow a standardized physiotherapy protocol as suggested by Ratajczak et al. (2019) and the AO Trauma group (<https://www.aofoundation.org/trauma>), detailed below:

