**Stage 1: First 3 weeks, starting 24 hours after surgery**

- Immobilization with a sling for the operated limb without weight-bearing.
- Initiation of pendulum exercises.
- Assisted passive movements.
- Avoid external rotation during the first 6 weeks.

**Stage 2: Third to ninth week, provided there are no abnormalities in consolidation or secondary displacement of fragments**

- Assisted active exercises, including flexion and abduction of the shoulder joint.
- Careful active exercises with limb abduction until pain occurs, with no weight-bearing in the first 6 weeks. Gradual weight addition will follow.

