**Stage 3: After the ninth week**

- Isotonic, eccentric, and concentric exercises.
- For participants with radiographic fracture consolidation (evaluated at the 12th week) and joint contracture, passive stretching exercises will be recommended under the guidance of an experienced professional.

Participants will attend 30-minute physiotherapy sessions twice weekly for 12 weeks.

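### Maximum lateral rotation of the operated shoulder is measured at four visits inside the six weeks in which the physiotherapy programme says to avoid external rotation

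*Protocol*

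**What the plan says.** Section 4.15.2 lists six shoulder movements for the ROM assessment: "The maximum tolerated positions in extension, flexion, abduction, adduction, lateral rotation, and medial rotation will be recorded by the evaluator". Both shoulders are measured. The timing is split by mode: "The ROM assessment will be performed 1 day after surgery and subsequently at 1 and 2 weeks through passive movements", and then "During evaluations at 4, 8, and 12 weeks, active movements will be assessed". The only condition placed on rotation is the starting position of the arm, at 0° of abduction and flexion.

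Section 4.11 sets the postoperative programme for both arms: "All participants will follow a standardized physiotherapy protocol". Its first block is headed "Stage 1: First 3 weeks, starting 24 hours after surgery". That block includes "Assisted passive movements" among what is allowed, and also the instruction "Avoid external rotation during the first 6 weeks". The section closes with the delivery schedule: "Participants will attend 30-minute physiotherapy sessions twice weekly for 12 weeks".

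**The concern.** Lateral rotation and external rotation are the same movement. Read together, the two sections tell the care team to keep the operated shoulder out of external rotation for six weeks, and tell the examiners to take it to its tolerated maximum four times in that period.

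Participant safety comes first: a research measurement takes a recently plated shoulder into a movement that the trial's own programme restricts. The only stated stop is what the participant tolerates. On day 1 that tolerance is judged after 24 hours of scheduled intravenous dipyrone and tramadol (section 4.9).

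Uniformity of the data is a second matter. Section 4.2 names four examiners. Faced with two instructions that disagree, one may measure fully, another may stop short and a third may leave the field blank. The calibration in section 4.3 gives no rule for this case.

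**Working it through.** The protocol gives no figure of its own on this point, so the check compares the ROM schedule with the restriction and then counts readings.

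**Inputs**
- ROM visits: day 1 and weeks 1, 2, 4, 8 and 12 (section 4.15.2).
- Mode: passive at day 1 and weeks 1 and 2; active at weeks 4, 8 and 12 (section 4.15.2).
- Restriction: the first 6 weeks, in a programme starting 24 hours after surgery (section 4.11).
- Participants: 42 (section 4.5).

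**Visits against the restriction**

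| Visit | Mode | Inside the 6 weeks? |
| --- | --- | --- |
| Day 1 | passive | yes |
| Week 1 | passive | yes |
| Week 2 | passive | yes |
| Week 4 | active | yes |
| Week 8 | active | no |
| Week 12 | active | no |

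So 4 of 6 visits fall inside the window.

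**Readings (operated side, lateral rotation, all 42 measured at every visit)**
- All visits: 42 × 6 = 252.
- Inside the window: 42 × 4 = 168, of which passive 42 × 3 = 126 and active 42 × 1 = 42.
- Outside the window: 42 × 2 = 84, and 252 − 168 = 84 agrees.

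These are upper bounds, since dropout can only lower them. They count measurements and say nothing about risk.

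**Does anything in the text reconcile the two sections?**
- The 0° position fixes where the arm starts, not how far it rotates.
- Passive handling does not resolve it at day 1 and weeks 1 and 2, because the Stage 1 list permits assisted passive movement and still bars this one.
- The week-4 reading is active. Stage 2, which then applies, names flexion and abduction and does not lift the six-week rule.
- Neither section refers to the other.

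The strength test shows what a compatible schedule looks like. Section 4.11 rules out weight-bearing for the first six weeks, and section 4.15.3 places the dumbbell test only at weeks 8 and 12. The protocol does not say whether this was deliberate.

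**The case against.** The strongest reply is about scope. The restriction is one item in a physiotherapy list, delivered in twice-weekly sessions by a physiotherapist, and it repeats a published rehabilitation programme that the protocol summarises. Section 4.15.2 governs something different: brief goniometer readings by trained orthopedic examiners. Nothing says that an exercise rule binds an examination. The readings also stop at what the participant tolerates, and the change from passive to active broadly follows the rehabilitation stages.

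This reading is possible, but three features of the text count against it. The same list contains sling immobilization, which is a standing precaution and not a session exercise. The rule runs for six weeks although the stage that contains it lasts three. And where pain is the intended stop, section 4.11 says so, for abduction; for external rotation the word is avoid.

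A second reply is that the visit forms (Appendices 3 to 8) and the figures are not available, and the forms may already omit the movement. That stands as a limit on the claim. It would not cure the conflict between two visible sections, since section 4.15.2 would still need to match the forms.

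A third reply is that no danger has been shown. That also stands. The documents report no harm and give no risk estimate for a single tolerance-limited reading after locked-plate fixation. Whether such a reading is safe is for the surgeons to decide.

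Finally, dropping four visits for this movement costs data on an outcome that section 3.2 wants followed over time. That is a fair point about the choice of remedy, and it is why an exception route is offered below.

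**Conclusion.** The concern holds as a minor, potential safety conflict. As written, four of six ROM visits, and at most 168 of 252 operated-side lateral-rotation readings, fall inside a period in which the trial's own programme says to avoid that movement, with no visible exception or limit in degrees.

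The conclusion rests on two assumptions: that the restriction is a general precaution and not one for exercises alone, and that the unseen forms do not already exclude the movement. Confidence is moderate for these reasons. It concerns one of six movements in one secondary outcome. The primary outcome, the sample size and the randomization are not affected.

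**What to change.** Add one sentence to section 4.15.2: *Lateral rotation of the operated shoulder will be measured only at weeks 8 and 12.* Then check Appendices 3 to 8 and bring them into line.

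The editing cost is small, but there is a data cost. Four early operated-side readings per participant are lost for this movement, including the day-1 value. Two per participant remain (at most 84 of 252), both active, so the time course and the comparison with the unaffected limb start at week 8. The other five movements keep all six visits.

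Alternatively, ask the surgeons whether early, tolerance-limited assessment of lateral rotation is safe. If they confirm that it is, write that exception, with a limit in degrees that they set, into both section 4.11 and section 4.15.2. This loses no readings and also removes the contradiction. The protocol supplies no such limit, so the figure has to come from the surgeons.
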